8. Outcome assessments: Each subject will have a 12-month follow up period, during which blinded research assistants will assess outcome measures. Follow-up data collection will begin 2 months after baseline because a full, 6-session course of PSE typically lasts 6-8 weeks. To limit attrition, we will employ a combination of monetary incentives and postcard reminders. Through these strategies, approved by the BUMC IRB in our pilot work, we have been able to maintain follow up rates > 85% across all relevant ongoing studies (there is a separate section on participant compensation in the protocol manual).

Baseline, 6-month, and 12-month assessments will take place in person with a staff RA. We will administer the QIDS and mental health service use questions on a bimonthly basis throughout the study period, and this will be done by telephone by a staff RA.

The 6-month interview will comprise the following valid and reliable scales:

- a. Perceived Stress Scale
- b. M.I.N.I. Depression Module
- c. QIDS
- d. Mental Health Service Use questions (adapted from Collaborative Psychiatric Epidemiology Surveys)
- e. Social functioning (Social Adjustment Scale-Self Report)
- f. Parenting Stress Index
- g. Problem Solving Questions (Social Problem Solving Inventory)
- h. Coping Questions (Brief COPE)
- i. Pearlin Mastery Scale
- j. Behavioral Activation for Depression Scale
- k. Rosenberg Self-Esteem Scale

The 12-month interview will comprise the following valid and reliable scales:

- a. Perceived Stress Scale
- b. M.I.N.I. Depression Module
- c. QIDS
- d. Mental Health Service Use questions (adapted from Collaborative Psychiatric Epidemiology Surveys)
- e. Social functioning (Social Adjustment Scale-Self Report)
- f. Problem Solving Questions (Social Problem Solving Inventory)
- g. Coping Questions (Brief COPE)
- h. Pearlin Mastery Scale
- i. Behavioral Activation for Depression Scale
- j. Rosenberg Self-Esteem Scale
- k. Recent Life Changes Questionnaire

- I. Mood, anxiety and alcohol and other substance use, modules of the SCID

RA's will be trained not to leave telephone messages, and to introduce themselves as from "BMC" so as to ensure confidentiality.

9. At 6-months post randomization, parents and Head Start teachers will be asked to fill out the Social Skills Rating System (SSRS) with reference to all 3-5 year-old Head Start children of enrolled parents.
10. We will assess rate of absenteeism from Head Start for children of mothers who are in our study.

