## Appendix – January 2018

The following appendix summarizes the content of an official letter written by the study PI to the National Institute of Mental Health in April 2010, specifying mediation and moderation analyses that were not included in the original grant application, in response to the NIH study section's summary statement (March 2010). This letter was requested by Program Official, [name]. The following summarizes the content of that letter. The letter itself is located in the study binder.

We outline an augmented analytic strategy to assess factors that have sound theoretical bases to either moderate or mediate the effect of PSE.

- a. *Theory based moderators:* Individual coping styles can substantially modify the effect of a problem solving intervention, as can the degree of baseline depressive symptoms. We proposed evaluate moderation by these factors by performing stratified analyses, followed by formal testing of interaction terms in our statistical models.
- b. *Theory based mediators:* According to our theoretical model (the Relational Problem Solving Model of Stress), improved problem solving skills and decreased perceptions of stress constitute likely intervention mediators; however, studies of other problem solving interventions have demonstrated impact in the absence of improved problem solving skills, problem resolution, or increased sense of mastery and self-control. Given PSE's emphasis on goal setting and action planning, a plausible alternative mechanism is behavioral activation, which we proposed to assess through the Behavioral Activation for Depression scale. We proposed to examine mediational effects using two potential techniques: the approach of Baron and Kenny and the use of path analysis models.

We detailed specific measures to reflect these constructs; each of these measures is listed in the main body of the trial protocol.

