| Construct                               | Measure                                                                                                                                                                                                                                                                                     | Hypotheses                                                                                                                                                                                                                                                         |
|-----------------------------------------|---------------------------------------------------------------------------------------------------------------------------------------------------------------------------------------------------------------------------------------------------------------------------------------------|--------------------------------------------------------------------------------------------------------------------------------------------------------------------------------------------------------------------------------------------------------------------|
| Behavioral Activation                   | The Behavioral Activation for Depression Scale (BADs) addresses four dimensions: activation, avoidance/rumination, work/school impairment, and social impairment; this measure thus spans the affective and functional domains.                                                      | Behavioral activation will partially mediate the effect of the intervention, particularly with regard to functional outcomes.                                                                                                                                      |
| Mastery / Self-esteem                   | The Pearlin Mastery Scale , which measures the degree to which individuals perceive themselves as in control of their lives,  will be used in conjunction with the Rosenberg Self-esteem Scale .                                                      | Self-perceived mastery will correlate with depression symptoms and problem solving orientation. Mastery will be impacted by intervention exposure but will not mediate its effect.                                                                                 |

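### A Baron and Kenny analysis of mastery alone cannot fairly test the prediction that mastery does not mediate; a joint path model on scales already collected can do better

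*Protocol*

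**What the plan says.** The Mastery / Self-esteem row of the table in the protocol's Appendix – January 2018 makes three predictions. The first is an association: "Self-perceived mastery will correlate with depression symptoms and problem solving orientation". The second and third share one sentence: "Mastery will be impacted by intervention exposure but will not mediate its effect".

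On method, the appendix text above the table says "We proposed to examine mediational effects using two potential techniques: the approach of Baron and Kenny" and, as the second technique, "the use of path analysis models". It does not say which applies to which hypothesis, or whether mediators are entered one at a time or together.

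Other mediators are proposed alongside. The appendix text says "improved problem solving skills and decreased perceptions of stress constitute likely intervention mediators", and the table adds "Behavioral activation will partially mediate the effect of the intervention, particularly with regard to functional outcomes".

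Under Procedure, the "Pearlin Mastery Scale", the SPSI-R, the BADS and the Perceived Stress Scale are each listed for baseline, 6 and 12 months. Depression is measured more often: "We will administer the QIDS and mental health service use questions on a bimonthly basis throughout the study period".

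**The concern.** Three statements are predicted to be true together: PSE changes mastery, mastery goes with depression, and mastery does not carry the effect of PSE. An analysis of mastery alone looks for the first two and, finding them, concludes against the third. The cell itself supplies an innocent reason for the association, because mastery is expected to track problem solving, which the appendix names as a likely mediator. A marker of the true mediator then looks like a mediator.

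The mastery row is the only one in the table that predicts no mediation. It therefore separates the theory behind PSE (problem solving, behavioral activation) from a general gain in sense of control. If the method tends to reject that prediction when it is true, the trial's statement on mechanism is unreliable. No primary result is at stake.

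**Working it through.** **Inputs from the protocol.** Sample Size Justification: 100 analyzable mothers per group, two-sided alpha 0.05, 80% power, standardized effect 0.4 (1 point / SD 2.5).

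**The plan's own figure.** A t-test for a 0.4 SD difference at 80% power needs 99.1, so about 100, per group; power at 100 is 0.804. The stated 100 per group is reproduced. The protocol gives no figure for mediation.

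**Can arm alone create the predicted correlation?** An effect of d SD correlates with arm at r = (d/2)/√(1 + d²/4). For d = 0.4 this is 0.2/√1.04 = 0.196. If mastery and QIDS both shift by 0.4 SD and are otherwise unrelated, the correlation arm induces is 0.196² = 0.038. With 200 mothers a correlation must reach about 0.14 to be significant. A mastery-QIDS correlation that the trial can see therefore nearly always survives adjustment for arm.

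**Scenario in which the hypothesis is true.** These values are assumptions, not protocol figures; within-arm variances are set to 1 and signs do not matter.
- PSE shifts SPSI-R by 0.4 SD.
- Mastery = 0.2 × arm + 0.5 × SPSI-R + noise.
- QIDS depends on SPSI-R with slope s = 0.3 to 0.5. Mastery has no effect on QIDS.

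**Mastery alone.**
1. Effect of PSE on mastery: 0.2 + 0.5 × 0.4 = 0.4 SD, detected with power 0.804.
2. Within-arm mastery-QIDS correlation: 0.5 × s, that is 0.15 to 0.25.
3. Power for that path, by Fisher's z with arm partialled out (√(200 − 4) = 14): at 0.15, z = 0.1511 × 14 = 2.116 and power = Φ(2.116 − 1.96) = 0.562. At 0.25, z = 0.2554 × 14 = 3.576 and power = Φ(1.616) = 0.947.
4. Both paths significant: 0.804 × 0.562 = 0.45 and 0.804 × 0.947 = 0.76. Simulation of the same model gives 44% and 76%.

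This counts the two mediator paths. If the full Baron and Kenny sequence is required, with a significant total effect (taken as 0.4 SD) and attenuation, simulation of the same scenario gives 36% to 64%.

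**SPSI-R in the same model.** The mastery path is now truly zero, so both mastery paths are significant in about 0.804 × 0.05 = 0.040, or 4%. Simulation agrees.

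**What the joint model does not cure.** If mastery and QIDS instead share an unmeasured cause (assumed correlation 0.2 to 0.5, PSE shift in mastery 0.4 SD, no mastery effect on QIDS), mastery is flagged in about 62-82% of trials alone and 65-82% jointly.

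**Reading a null result.** With a 0.4 SD shift in mastery and a true indirect share of 12% to 17% of the total effect, the mastery-to-QIDS path is detected with power of only 28% to 55%. A non-significant path is weak evidence of no mediation.

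**The case against.** The strongest reply is that path analysis is also named and can hold several mediators. A reader might infer that no planned result could support the mastery prediction. The documents do not bear that out: a joint path model giving a mastery-specific indirect effect near zero with a tight interval would support it, under a no-confounding assumption. This reply stands. It limits the criticism to the mastery-alone form, which the protocol leaves open.

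A reader might also infer that low power would often lead the trial to confirm the prediction wrongly. If PSE shifts mastery by 0.2 SD and mastery truly carries part of the effect (slopes 0.3 to 0.5), mediation goes undetected in 71-76% of trials. Nearly all of those misses arise because the effect of PSE on mastery is itself not significant, so the first half of the hypothesis fails as well. The pattern that would look like confirmation, mastery shifted but no path to QIDS, occurs in about 0-0.2% of trials at those slopes and about 6-13% at slopes of 0.15 to 0.2. Nor does the protocol say that a null path will be reported as no mediation.

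An effect on mastery plus an unadjusted correlation does not entail mediation by definition, and the protocol says mastery will be affected, not that it will rise. Both points are right. The first matters little in practice, given the 0.038 above.

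Finally, the choice of path model is commonly left to the SAP, which is not shown, so its absence is no finding. What remains is that one technique the protocol does name is ill suited, when used on mastery alone, to a prediction the protocol also states.

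**Conclusion.** The point holds in limited form. Applied to mastery alone, the Baron and Kenny approach is not a fair test of the prediction that mastery does not mediate, because the appendix's other two predictions for mastery are what that approach takes as evidence of mediation. Where the mastery-QIDS link runs only through problem solving, false mediation appears in about 44-76% of trials, against about 4% with SPSI-R in the model.

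The range rests on assumed values: SPSI-R effect 0.4 SD, SPSI-R-QIDS slope 0.3 to 0.5, mastery-SPSI-R slope 0.5, and QIDS as the outcome. It would change with other values. The contrast between the two analyses holds across the slopes tried, but only when the link runs through a measured mediator; unmeasured common causes defeat both. The hypothesis itself is sound and needs no rewriting. The matter is secondary and touches neither the primary analyses nor the sample size.

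**What to change.** Keep the mastery hypothesis and name the analysis that tests it, in the appendix or the SAP:
- one path model with mastery, SPSI-R, BADS and Perceived Stress entered together and their baseline scores as covariates, in place of Baron and Kenny steps for mastery alone;
- each indirect effect, and the difference between the mastery and problem-solving indirect effects, reported with bootstrap 95% confidence intervals;
- a statement that a non-significant mastery path will not be reported as absence of mediation;
- a statement that the joint model does not remove unmeasured common causes of mastery and depression, so the mastery path remains subject to a no-confounding assumption.

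The cost is a few sentences and one model. All four scales are already scheduled at baseline, 6 and 12 months, so no new data collection is needed.
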